**Methods:**

RADAR-MDD is a multi-site prospective cohort study, aiming to recruit 600 participants with a history of depressive disorder across three sites: London, Amsterdam and Barcelona. Participants will be asked to wear a wrist-worn activity tracker and download several apps onto their smartphones. These apps will be used to either collect data passively from existing smartphone sensors, or to deliver questionnaires, cognitive tasks, and speech assessments. The wearable device, smartphone sensors and questionnaires will collect data for up to 2-years about participants’ sleep, physical activity, stress, mood, sociability, speech patterns, and cognitive function. The primary outcome of interest is MDD relapse, defined via the Inventory of Depressive Symptomatology- Self-Report questionnaire (IDS-SR) and the World Health Organisation’s self-reported Composite International Diagnostic Interview (CIDI-SF).

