**Fig. 1 Fig1:**
[figure not shown]
Participant flowchart

Recruitment procedures will vary slightly across sites. Potentially eligible individuals will be identified either through existing research cohorts (in London and The Netherlands) who have given consent to be contacted for research purposes, or through mental health services (in London and Barcelona). These individuals will be contacted by a member of the on-site research teams and sent the study information sheet and consent from. Those who provide verbal consent to participate will have a more detailed conversation with the research teams, during which they will have an opportunity to ask questions about the study, have their eligibility confirmed, and arrange a suitable time for enrolment.

Enrolment will either happen at the research centre, or at the participant’s home depending on the site they have been recruited from. Participants will receive a £15/€20 for enrolling in the study, and £5/€10 for every three months of continued participation. Participants who take part in additional qualitative interviews at 3-month or 1-year follow-up will receive £10/€10 per interview. Written consent will be obtained, during the enrolment session, which will include collection of sociodemographic, social environment, medical history and technology use questionnaires, and lifetime depression history measured through the Lifetime Depression Assessment – Self-Report (LIDAS [34];), alongside baseline data collection of all outcome measures via Research Electronic Data Capture (REDCap) software [35].

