#### Passive RMT (pRMT) app

All modern smartphones comprise the sensors required for measurement in RADAR-MDD, however our study will only incorporate Android smartphones. For participants who do not use a smartphone, we will offer to provide a suitable smartphone for them. Participants who are using a non-Android smartphone will not be recruited unless they explicitly state that they are willing to switch to an Android smartphone as their only phone for the duration of follow-up, and in these cases an appropriate phone will be provided. Each participant will be asked to install the purpose-built pRMT application. This will run in the background, requiring minimal input from participants, collecting data on ambient noise, ambient light, GPS location, keystokes (at the London site only), Bluetooth connectivity, length and duration of calls, number of text messages and emails and weather conditions, in addition to battery life. GPS location data will be obfuscated; that is, providing relative location data, not absolute coordinates, preventing identification of an individual’s home address or precise geographical location.

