### Statistical and analysis plan

Descriptive statistics for demographics, attrition rate, and number of participants using the remote assessment measurements without loss or damage and providing adequate data for the duration of the study period will be estimated. Using classification/regression approaches, we will investigate whether any demographics and/or other numerical information obtained during baseline of the study might serve as a predictor for subjects drop out/percentage of adequate data. Using mixed-effect models with participants as random factor, we will estimate whether relationships between the amount of usable data during the weeks prior to the outcome assessment and obtained scale’s measurements exist.

Aggregated features obtained from biosensors, smartphones, cognitive tests and from ESM, as well as their changes from baseline or previous time points (delta features) will be used for statistical analysis. Aggregation will be done for the period of 2 weeks prior to participant’s evaluation with PHQ8 or longer time interval preceding 3-mothly outcome scale assessment, since relapse identification is done retrospectively. First, univariate approach, where each variable/feature will be modelled with use of mixed-effect models, with depressive relapse as fixed and participant as random effect, to find out which variables are influenced during the relapse. Demographics and other baseline characteristics will be added to the model, when necessary, with correction for multiple comparisons.

Secondly, we will construct predictive models, using aggregated data obtained prior to assessment of relapses and their changes from previous time points to predict binary (relapsed or not) or continuous (when scale score is treated as continuous variable) outcomes. Under assumption that data are missing at random, multiple imputation will be applied for covariates, where missing-ness is not drastically high. Multivariate prediction model will be constructed and variable selection, based on, for example, LASSO L1-regularization for linear models, or different feature selection algorithms will be applied. Models’ performance will be characterized through the cross-validation, putting stress on sensitivity and specificity of relapse prediction model.

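### For level features, the single relapse coefficient mixes within-person change with differences between people, yet it is read as change during relapse

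*Protocol article*

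**What the plan says.** The Statistical and analysis plan section of the protocol article sets out two steps. In the first, each feature is the outcome of its own mixed-effects model, "with depressive relapse as fixed and participant as random effect, to find out which variables are influenced during the relapse". On covariates it adds: "Demographics and other baseline characteristics will be added to the model, when necessary, with correction for multiple comparisons". The features enter both as aggregated levels and as changes, "as well as their changes from baseline or previous time points (delta features) will be used for statistical analysis". The second step builds multivariable models that predict relapse. The Outcome measurements section sets assessments at baseline and every three months for up to two years, so there are at most 24/3 = 8 follow-up assessments per person. Under Study population, people may enter with or without current depressive symptoms.

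**The concern.** Asking which variables are affected during relapse is asking how a person in relapse differs from the same person out of relapse. Relapse status varies over time, but the share of assessments spent in relapse also differs between people. A model with a participant random intercept and one relapse coefficient uses both sources of variation. Its coefficient equals the within-person effect only if a person's usual feature level is unrelated to how often that person relapses, or if the between-person and within-person effects happen to be equal.

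That independence is doubtful here. The cohort mixes people who are ill at entry with people who are well, and usual sleep, activity or sociability may well differ between those who spend much of follow-up depressed and those who do not. At stake is the list of features declared to change during relapse: some could be on it because relapse-prone people differ at all times.

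**Working it through.** **The plan's own figure.** The article gives no figure for this step. Its one sample-size calculation (100 relapses at 33% a year: 100/0.33 = 303, stated as 300) concerns the prediction model and is not affected.

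**Inputs.** From the article: 600 participants, up to 8 follow-up assessments, one relapse term, participant as random effect (read as a random intercept). Assumed, because the article does not give them: feature ICC, relapse ICC (rho), the correlation between usual feature level and relapse propensity, and n = 4 as a case with half the assessments available.

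**Weight on the between-person difference.** The coefficient is w × between + (1 − w) × within, with

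- k = (1 − ICC) / [(1 − ICC) + n × ICC]
- B = rho + (1 − rho)/n (between-person variation in relapse)
- W = (1 − rho)(1 − 1/n) (within-person variation in relapse)
- w = kB / (W + kB)

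Lowest case (ICC 0.7, n = 8, rho 0.2): k = 0.3/5.9 = 0.051, B = 0.30, W = 0.70, w = 0.0153/0.7153 = 0.021.

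Highest case (ICC 0.1, n = 4, rho 0.4): k = 0.9/1.3 = 0.692, B = 0.55, W = 0.45, w = 0.381/0.831 = 0.458.

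| Feature ICC | n = 8, rho 0.2 | n = 8, rho 0.4 | n = 4, rho 0.2 | n = 4, rho 0.4 |
|---|---|---|---|---|
| 0.7 | 2.1% | 4.4% | 6.1% | 10.6% |
| 0.5 | 4.5% | 9.1% | 11.8% | 19.6% |
| 0.1 | 18.5% | 32.4% | 31.6% | 45.8% |

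**False positives.** The simulation used 600 participants, 4 or 8 assessments, feature SD 1, ICC 0.3 to 0.7, a correlation of 0.3 or 0.5 between stable level and relapse propensity, about 13% of assessments in relapse, a true within-person effect of zero, and 400 replicates per scenario.

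| Analysis | Coefficient (SD units) | Rejection at nominal 5% |
|---|---|---|
| Model as written, level features | 0.013 to 0.112 | 7.5% to 52% |
| Within-person deviation only | about 0 | 3% to 7% |
| Model as written, change-from-baseline features | about 0 | 4% to 7% |

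The weights in these runs were 1.4% to 15.5%. With more heterogeneous relapse propensity (logit SD 2 instead of 1; ICC 0.5, 8 assessments) the coefficient was 0.049 to 0.083 SD and rejection 33% to 74%.

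Two runs show the limits. With no correlation between usual level and propensity (ICC 0.5, 8 assessments), the coefficient was 0.002 and rejection 6.0%. With 300 participants (ICC 0.5, 8 assessments, correlation 0.3), the coefficient was 0.025 but rejection only 5.8%. The Monte Carlo standard error at 5% is sqrt(0.05 × 0.95/400) = 1.1 percentage points.

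**The case against.** The strongest reply is that the plan already contains a within-person analysis. It also uses delta features, and a stable personal level cancels in a change score; the simulation confirms this. That stands, and it limits the point to level features. It does not dispose of it, because the deltas are used in addition to the levels, and both are read as showing what relapse influences. For someone depressed at entry, change from baseline is also measured against a depressed reference, so it does not fully replace a within-person contrast.

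A second reply is that the random intercept already removes most of the between-person difference. This is correct. In the main simulations a pooled comparison without it gave 0.145 to 0.378 SD, against 0.013 to 0.112 SD with it. A reader might infer that stable differences pass whole into the relapse effect. They do not: they are down-weighted, and without a correlation between level and propensity there is no bias.

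A third is that this step is a univariate screen. The prediction models have their own variable selection and cross-validation, the text does not make entry depend on the screen, and stable differences between people are legitimate information for prediction. This also stands, so the predictive aim is not in question.

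A reader might further infer that leaving out a site term is an error, given that "Recruitment procedures will vary slightly across sites", that payments differ by currency and that one data stream is collected in London only. The documents do not support that. The text neither names nor excludes site, baseline characteristics may be added, and a condensed article can leave the covariate list to a fuller plan. A site term would not cure the problem either: the coefficient was 0.042 with and without it (ICC 0.5, correlation 0.5, 8 assessments). The payment amounts and the London-only stream show no error in the analysis.

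**Conclusion.** The point holds for level features. The article fixes both the model and a within-person reading of it, and the two do not match, so this is more than detail left to a later plan. Under the assumed values, 2% to 20% of the weight falls on between-person differences at feature ICC 0.5 to 0.7, and up to 46% at ICC 0.1 with four assessments. The bias is modest in SD units, but with 600 participants it can lift the false-positive rate well above 5%. Correction for multiple comparisons adjusts the threshold and leaves the bias in place.

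A reader could multiply the 46% weight by an assumed between-person difference of 0.5 SD and quote a spurious effect of 0.23 SD. That should not be the headline, since it needs the lowest ICC, the fewest assessments and the highest relapse ICC together, and none of these is in the documents.

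The direction of the argument is secure if usual level and relapse propensity are correlated. The size rests wholly on assumption, and it shrinks with more assessments per person and with higher feature ICC.

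**What to change.** In the univariate mixed models for level features, replace the single relapse term with two: the participant's mean relapse status (share of assessments in relapse) and the deviation of each assessment from that mean. Base the statement about what is influenced during relapse on the deviation term, and report it beside the delta-feature results. The person-mean term can be reported separately as the between-person association.

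The cost is one extra term per model and a wider interval for the within-person effect. The standard error is multiplied by 1/sqrt(1 − w):

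- w = 0.021: 1.01
- w = 0.196: 1.12
- w = 0.458: 1.36

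That is about 1% to 12% wider for ICC 0.5 to 0.7 and up to about 36% in the extreme low-ICC case. The loss is largest exactly where the mixing is worst, so it should be stated openly.

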### Study objectives

RADAR-MDD is a clinical study aiming to assess the utility of multi-parametric RMT in clinical populations with MDD.

Specifically, RADAR-MDD aims to:Determine the usability, feasibility and acceptability of, and adherence to, RMT to provide real-time objective multidimensional indications of clinical state in individuals with MDD.Improve and refine clinical outcome measurement using RMT as a means of identifying current clinical state.Determine whether multi-parametric RMT collected in populations with recurrent MDD can provide information predictive of depressive relapse and other critical outcomes including anxiety, quality-of-life, and MDD remission.

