### Study population

An estimated 100 relapses are required in order to provide sufficient power on which to test the predictive utility of RMT, if 10 variables were entered into the predictive model [32]. With an approximated annual relapse rate of 33% (a lower estimate than that provided in the Star*D trial; [33]), 300 participants would be required, followed-up for one year. Although there is evidence to suggest promising uptake to RMT protocols, the attrition rate in this length of follow-up is unknown, there are likely to be missing data, data are inherently “noisy”, and the relapse rate in our population may be lower than anticipated. We therefore aim to recruit a total of 600 individuals with a history of MDD across three research sites.

The eligibility criteria for inclusion in this study are summarised in Table 1. To recruit people at risk of relapse during the follow-up period, people with a recent history of MDD, with indication of a recurring trajectory will be approached to participate. No limitations have been applied regarding any treatment they may be receiving, although medication use and other psychological interventions will be monitored throughout the course of follow-up. Additionally, participants will be eligible to participate regardless of whether they are currently experiencing depression symptoms or not.

**Table 1 Tab1:** Eligibility criteria for participation in RADAR-MDD

Inclusion criteria	Exclusion criteria
Meet DSM-5 diagnostic criteria for diagnosis of non-psychotic MDD within the past 2 years. Recurrent MDD (a lifetime history of at least 2 episodes of depression; (LIDAS) [34]). Willing and able to complete self-reported assessments via smartphone. Able to give informed consent for participation. Fluent in English, Spanish, Catalan or Dutch language Existing ownership of Android smartphone or willingness to use an Android smartphone as their only smartphone. Aged 18 or over	Lifetime history of bipolar disorder, schizophrenia, MDD with psychotic features, schizoaffective disorders. Dementia History of moderate to severe drug or alcohol dependence within the last 6 months History of major medical disease which might impact upon the patient’s ability to participate in normal daily activities for more than 2 weeks (e.g. due to likely hospitalisations or other periods of indisposition). Pregnancy

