#### Active RMT (aRMT) app

Following extensive focus group work and user testing [31], an additional app has been created to administer the aRMT aspects of the study protocol. This includes validated questionnaires to measure depressive symptoms and self-esteem. Variability of depressive symptoms will be measured via the 8-item Patient Health Questionnaire (PHQ8; [38]) every 2 weeks throughout the course of follow-up. Variation in self-esteem will be measured using the Rosenberg Self-Esteem Scale; RSES [39]. The RSES is a widely-used 10-item self-reported questionnaire used to quantify self-esteem along a continuum and will be administered alongside the PHQ8 every 2 weeks.

As with the PHQ8 and RSES, every 2- weeks participants will be asked to complete a speech task. This requires participants to say aloud, in a quiet area, some excerpts from “The North Wind and the Sun”, which are shown to be phonetically balanced across all three languages [40]. These will be offered on a random schedule to prevent rehearsal and fluency and preserve prosodic features. In addition to this, participants will be asked to respond to the following question: “Can you describe something you are looking forward to this week?”

The aRMT app will also deliver an ESM schedule (see online Additional file 1), which has been designed to collect brief, in-the-moment assessments relating to several of our domains of interest: mood, stress, sociability, activity and sleep. Participants will receive a series of questions intended to reflect their current state (such as “right now, I feel content”), with 7-point Likert scale answer options (0 = Not at all, 7 = Very much). The ESM schedule consists of approximately 44 items, taking up to 3-min to complete, delivered 9 random times per day within 90-min blocks starting from 08.30 and ending at 22.00 for 6 consecutive days every 6 weeks.

Cognitive function will also be measured using the THINC-IT® app, which has been specifically designed and validated to screen for cognitive dysfunction in depression [41], and includes assessments of elements of executive function such as memory, concentration, and attention.

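### The relapse prediction model has no symptom-score reference model, so as written the analysis would not show whether RMT features add to severity already known from IDS-SR and PHQ8

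*Protocol article*

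**What the plan says.** Aim 3 under Study objectives is to "Determine whether multi-parametric RMT collected in populations with recurrent MDD can provide information predictive of depressive relapse" and other outcomes. The Statistical and analysis plan section pursues it in two steps. The first fits univariate mixed models, to which baseline characteristics may be added if needed. The second builds multivariable models from aggregated features and their changes since earlier time points, "to predict binary (relapsed or not) or continuous (when scale score is treated as continuous variable) outcomes". The feature sources named are biosensors, smartphones, cognitive tests and the experience sampling (ESM) schedule. Performance is to be characterised by cross-validation, with stress on sensitivity and specificity.

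The section names no reference model, no difference in performance and no benchmark. PHQ8 appears in it only as the anchor of the two-week aggregation window.

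Four facts elsewhere in the article bear on this:
- The ESM schedule is meant to "collect brief, in-the-moment assessments relating to several of our domains of interest: mood, stress, sociability, activity and sleep", so part of the RMT input is self-reported mood.
- Under Study population, people are eligible with or without current depressive symptoms.
- Under Primary outcome, the event is MDD by CIDI-SF together with an IDS-SR score above 25. The definition as printed mentions no preceding well period.
- PHQ8 is collected every two weeks. IDS-SR and treatment are collected at baseline and every three months, and lifetime depression history at enrolment.

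**The concern.** Current severity should be a strong predictor of meeting the outcome at the next assessment. Entry status is mixed and the outcome itself contains a severity threshold. When the outcome is the continuous scale score, the previous value of the same scale is an obvious predictor. ESM mood items measure severity directly. The Background reports that sensor data change with depressive episodes, so passive features can track severity as well.

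A model that only recovers the last questionnaire score would therefore show sensitivity and specificity better than chance. A criterion that looks at this model alone gives the same kind of result whether RMT adds much, a little or nothing to what a questionnaire already shows.

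At stake is the interpretation. The closing paragraph of the Discussion looks to a conclusion about the clinical utility of RMT for predicting relapse. The Discussion also presents RMT as an answer to infrequent, subjective outcome measures. Those are comparative claims, and absolute accuracy does not support them.

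**Working it through.** **1. The plan's own figure.** The plan states "An estimated 100 relapses are required in order to provide sufficient power" "if 10 variables were entered into the predictive model", which implies 100 / 10 = 10 events per variable. At the stated 33% annual relapse rate, 100 / 0.33 = 303 participants, and 300 × 0.33 = 99 relapses. The stated "300 participants would be required, followed-up for one year" is reproduced within rounding and is not in dispute.

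**2. How well a pure proxy can look.** All inputs here are assumptions. In a binormal model, let prior severity alone have AUC 0.75. Its separation is d' = √2 × z(0.75) = 0.954. A score that is a noisy copy of severity with correlation r, and nothing else, has separation 0.954r and AUC = Φ(0.954r / √2):
- r = 0.4: AUC 0.61
- r = 0.6: AUC 0.66
- r = 0.8: AUC 0.71

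**3. Check by simulation.** All inputs are again assumptions. Relapse (about 33%) depends on a previous symptom score S with log-odds 1.2 per SD. An RMT composite R correlates with S and has no effect of its own. Large-sample results:

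| Correlation of R with S | AUC, R alone | Sensitivity / specificity, R alone | AUC, S alone | AUC, S + R |
|---|---|---|---|---|
| 0.5 | 0.64 | 0.61 / 0.58 | 0.776 | 0.776 |
| 0.7 | 0.69 | 0.66 / 0.62 | 0.776 | 0.776 |
| 0.9 | 0.75 | 0.68 / 0.68 | 0.776 | 0.776 |

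Across log-odds of 0.8 to 1.6 per SD and the same correlations, R alone spans AUC 0.60 to 0.79. At a correlation of 0.3 it falls to 0.56 to 0.59.

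At N = 300 (log-odds 1.2, correlation 0.5), R alone is significant at the 5% level in 97% of runs, although it adds nothing. The likelihood-ratio test of S + R against S rejects in 6%, close to nominal. The comparison with S is what tells the two situations apart.

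**4. Power for the gain.** In the same setting, let R have its own effect per SD:
- 0.3 log-odds: power of the added-value test is about 47% at N = 300 and 75% at N = 600 with no attrition.
- 0.5 log-odds: about 86% and 99%.

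This treats R as one composite with one degree of freedom. A selected set of several features may have less power.

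**5. Events budget.** The plan states "We therefore aim to recruit a total of 600 individuals with a history of MDD across three research sites". Then 600 × 0.33 = 198 relapses are expected in one year before attrition. Keep the 10 RMT variables and the implied 10 events per variable:
- Five reference terms: 15 × 10 = 150 events, 150 / 0.33 = 455 participants. This fits if losses stay below 1 − 150/198 = 24%.
- Six terms (three sites take two indicators): 16 × 10 = 160 events, 160 / 0.33 = 485 participants. This fits if losses stay below 1 − 160/198 = 19%.

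The plan gives no attrition rate and says it is unknown. Follow-up runs for up to two years, so one year's events are not the ceiling.

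**The case against.** The strongest objection is that aim 3 asks only whether RMT carries information predictive of relapse, not whether it adds to a questionnaire. A passive signal that follows severity between assessments, without burdening the patient, could be useful even if it adds nothing to a questionnaire. This stands. It is why absolute prediction may remain the main result, and why the reference model is asked for alongside it.

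Second, the article is condensed and the full analysis plan is not shown, so a reference model may be specified there. This limits confidence. But the article does fix the feature sources and the performance criterion, and that criterion by itself does not support the utility conclusion.

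Third, the split between RMT and questionnaires is not the protocol's own, since PHQ8 is delivered through the active RMT app. This stands, and the fix has to deal with it. The use of change features weakens the picture of a static copy of severity, but they accompany the levels and do not replace them.

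Two stronger readings are tempting, and the article supports neither:
- A reader might infer that the study cannot separate RMT information from symptom scores. It can: both are collected in the same people at known times.
- A reader might infer that sensitivity and specificity are the only measures planned. The text puts stress on them and does not exclude others.

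**Conclusion.** The point holds as a gap in the stated analysis, not in the design. As written, the analysis shows whether RMT features predict relapse. It does not show whether they add to severity already known from IDS-SR and PHQ8, and any claim of added clinical utility needs that.

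The AUC figures show how far a proxy could go under assumed effect sizes and correlations, with zero added information built in. They do not show that RMT features in this cohort are mere proxies. The direction does not depend on the exact inputs: a score correlated with a predictive severity measure will itself predict.

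The sample size reproduces and is not questioned. The change is worth making because it is cheap and uses data already planned. Confidence is moderate, because the full analysis plan might already contain it.

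**What to change.** Keep the planned performance measures and add the following.

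- Pre-specify a reference model from data already collected: previous IDS-SR, last PHQ8 before the prediction window, depression history, treatment and site.
- Fit it under the same cross-validation as the RMT model. Report the difference in performance when RMT features are added (for example in AUC or log-likelihood), with an interval.
- State on which side PHQ8 and the ESM mood items fall, and report passive-only features separately from self-reported ones.
- Let absolute prediction remain the main result for aim 3 if that is intended, and rest any claim of added clinical utility on the difference.

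The cost is one extra model and no new data collection. The gain will look smaller than absolute accuracy and will be estimated with less power. The reference terms use part of the events budget, about 150 to 160 of the roughly 198 relapses expected in one year, which leaves room for losses of about 24% or 19%.
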